### Objectives of the study

Two sets of objectives will be analyzed. The first will be analyzed after approximately 156 patients have been implanted with this new pacemaker system and followed for 4 months to provide data for Medtronic market release outside of the US and the second analysis is after approximately 470 patients have been implanted and are followed for 4 months after receiving this new pacemaker system for regulatory requirements purposes.

The first set of objectives related to the 156 patients implanted and followed-up is described below:

#### b) Secondary Objectives

All secondary objectives and additional analyses are analyzed using descriptive statistics but are not statistically evaluated.

1. Confirm that labelling instructions for completing the MRI scans were followed to ensure patient safety. Occurrence of system-related adverse device effects due to insufficiencies of the labelling or inadequacies of the labelling are used.

2. Characterize occurrence of sustained ventricular arrhythmias and asystole seen during MRI scans.

3. Characterize all implant procedure-, pacing system- and MRI procedure-related complications and observations to four months post-implant.

4. Summarize atrial and ventricular lead impedance up to four months post-implant.

5. Characterize the lead handling of the CapSureFix MRI lead model 5086 MRI in relation to the commercially available model 5076. A seven-point questionnaire is used.

6. Characterize four months pacing threshold and sense amplitude of the MRI group and control group in relation to the commercially available lead Model 5076.

#### c) Additional Analysis

1. Demonstrate that the EnRhythm MRI SureScan Pacing System (both generator and leads) can be identified as MRI-labelled with X-ray (Figure 2). A seven-point questionnaire is used.

**Figure 2 F2:**
[figure not shown]
Radiopaque labels on lead and IPG to identify that patient has an MRI-conditional system implanted.

The second analysis after 470 patients have been implanted and followed-up for four months contains the following objectives:

#### a) Primary Objectives

1. To assess if the MRI-related complication-free rate in the month following MRI is greater than 90%. A one-sided exact test with a 97.5% confidence interval is used for analysis.

2. To compare the changes in a) atrial and b) ventricular voltage thresholds at 0.5 ms before and one month after MRI/no-MRI between the MRI and control groups. The hypothesis will test whether the proportions of patients (p_1_and p_2_) that experience an acceptable threshold increase less or equal to 0.5 V are equivalent (Δ = 10%, p_1 _and p_2 _= 96%) between the two groups. The objective will be analyzed using a two-sample 97.5% confidence interval, with p-values from the Farrington-Manning test for equivalence of proportions.

3. To compare the changes in a) atrial and b) ventricular sense amplitudes before and one month after MRI/no-MRI between the MRI and control groups. The hypothesis will test whether the proportions of patients (p_1 _and p_2_) who experience a sense amplitude decrease less than 50% and whose sense amplitudes remain above an clinically acceptable minimum (1.5 mV for atrium and 5 mV for the ventricle) at one month post-MRI/no-MRI are equivalent (Δ = 10%, p_1 _and p_2 _= 93%) between the two groups. The objective will be analyzed using a two-sample 97.5% confidence interval, with p-values from the Farrington-Manning test for equivalence of proportions.

All 3 primary objectives of this second set need to be met in order to pass the study.

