### Sample size and data use for analysis

Sample size calculations for both sets of objectives exclude attrition and provide at least 80% power with a type one error rate (alpha) of 0.05 (first set) or 0.025 (second set). No alpha adjustment was necessary for the two analyses, since the objectives are different and both sets will each be analyzed only once. Sample sizes were calculated separately for each primary objective and the largest requirements (62 patients per group for the first set, 122 per group for the second set) were further increased to 156 and 470 total patients, respectively, for consideration of estimated study attrition and added regulatory requirements.

Pre-specified analysis exclusion criteria were listed in the investigational plan and include the following:

• Data from visits outside the 1 month post-MRI visit window are excluded from the primary analyses of capture and sensing objectives, but are included in a secondary sensitivity analysis of these objectives.

• Data from patients whose MRI scans were not performed according to protocol requirements are excluded from the analyses of capture, sensing, MRI-related complications, labeling instructions, occurrence of arrhythmias, and lead impedance.

• Data from patients in atrial arrhythmias at the time of electrical data collection are excluded from analyses of atrial capture and sensing objectives at affected visits.

• Data from patients with unresolved lead dislodgments are excluded from analyses of capture, sensing, and impedance objectives.

• Data from patients with a pacing threshold difference exceeding 0.5 V prior to the MRI visit, which is indicative of an abnormal lead/tissue interface, are excluded from analyses of capture and sensing objectives.

• Pacing capture data lacking required threshold strip documentation or not measured at 0.5 ms are excluded from the analysis of the capture threshold objective.

• Patients unable to capture will be assigned a capture threshold value of 6 V at affected visits for the purpose of calculating descriptive statistics.

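### Second-set sensing objective is worded as equivalence, but its 122 per group is the size for a one-sided, single-margin test

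*Protocol article*

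**What the plan says.** All of this is in the protocol article.

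- Primary Objectives for the second analysis, objective 3 (sensing): the hypothesis is that the two proportions "are equivalent (Δ = 10%, p_1 _and p_2 _= 93%) between the two groups".
- Same section, objective 2 (capture): the proportions "are equivalent (Δ = 10%, p_1 _and p_2 _= 96%) between the two groups".
- Both objectives carry the same analysis sentence: "The objective will be analyzed using a two-sample 97.5% confidence interval, with p-values from the Farrington-Manning test for equivalence of proportions". It does not say whether the interval is one- or two-sided, or whether one margin or both must be cleared.
- Objective 1 of the same list is directional (a rate above 90%) and pairs an explicitly one-sided exact test with a 97.5% interval.
- Sample size and data use for analysis: the calculations exclude attrition and "provide at least 80% power with a type one error rate (alpha) of 0.05 (first set) or 0.025 (second set"). The figures given are "62 patients per group for the first set, 122 per group for the second set", and these "were further increased to 156 and 470 total patients, respectively, for consideration of estimated study attrition and added regulatory requirements".
- Randomization: more than 60% of patients are expected to be allocated 1:1 and the rest 2:1.

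The second set passes only if all three of its primary objectives are met.

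**The concern.** Equivalence of two proportions ordinarily means that the difference must be shown to lie inside both margins. With the same inputs this needs more patients than showing that it lies above the lower margin only. The article states the hypothesis, margin, assumed rates, test, interval level, alpha, power and size, so the size can be checked against the hypothesis. It matches a one-margin test that the article never names; the term non-inferiority does not appear.

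Two things are at stake. First, the claim to "provide at least 80% power" is attached to a hypothesis that it does not describe. Second, for primary objectives in an unblinded trial, the number of margins to be cleared should not be left open until the data are in.

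**Working it through.** **Inputs.** Objective 3: p = 0.93 in both groups, margin 0.10. Objective 2: p = 0.96, margin 0.10. Alpha 0.025, power 80%, 122 per group before attrition, 470 enrolled.

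**Formula.** Farrington-Manning with equal groups:

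n per group = [z(1−α)·√V0 + z·√V1]² / 0.10²

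V0 is the sum of the two binomial variances at the maximum-likelihood rates restricted to a difference of −0.10. V1 = 2p(1−p). The second z is z(0.80) = 0.8416 for one margin. For both margins with equal true rates it is z(0.90) = 1.2816, because the 20% type II error is split between the two margins.

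**Step 1: reproduce 122 (sensing).** The restricted rates are 0.8556 and 0.9556.

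- V0 = 0.1236 + 0.0425 = 0.1660, √V0 = 0.4075
- V1 = 2 × 0.93 × 0.07 = 0.1302, √V1 = 0.3608
- One margin, one-sided 0.025: [(1.9600 × 0.4075 + 0.8416 × 0.3608)/0.10]² = 121.5, so **122**, the article's figure

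The same calculation for capture (p = 0.96) gives 88.4, so 89. Sensing therefore sets the 122.

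**Step 2: sensing size if both margins must be cleared.**

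- 0.025 per side: [(1.9600 × 0.4075 + 1.2816 × 0.3608)/0.10]² = 159.02, so **160** per group
- 0.0125 per side (both limits of a two-sided 97.5% interval): z(1−α) = 2.2414, giving 189.3, so **190** per group

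**Step 3: power at 122 per group.** Power to clear one margin is Φ(k), with k = (0.10·√122 − z(1−α)·√V0)/√V1. Power to clear both is 2Φ(k) − 1.

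Sensing:

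- 0.025 per side: k = 0.848, Φ = 0.802; both margins 0.603
- 0.0125 per side: k = 0.530, Φ = 0.702; both margins 0.404

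| Test at 122 per group | Sensing, 93% (exact) | Capture, 96% (exact) |
|---|---|---|
| One margin, one-sided 0.025 | 80% (82%) | 92% (94%) |
| Both margins, 0.025 per side | 60% (65%) | 85% (89%) |
| Both margins, 0.0125 per side | 40% (45%) | 71% (78%) |

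The exact values come from full binomial enumeration of the same test.

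**Step 4: the trial as enrolled.** Take 60% of 470 at 1:1 (282, so 141 and 141) and the other 188 at 2:1 (about 125 and 63). That gives about 266 MRI and 204 control patients. The article gives no attrition rate, so a range of equal losses in both groups is assumed. Sensing power for both margins, normal approximation:

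| Loss | 0.025 per side | 0.0125 per side |
|---|---|---|
| 0% | 95% | 90–91% |
| 10% | 92% | 86% |
| 15% | 90% | 82% |
| 20% | 88% | 78% |
| 30% | 81% | 68% |

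Power stays at or above 80% up to about 30% loss at 0.025 per side, and about 17–18% at 0.0125 per side.

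**The case against.** The strongest reply is that the article is coherent if equivalence is read loosely. Two-sample describes two groups, not two sides. Objective 1 in the same list pairs 97.5% with a one-sided test, and alpha is 0.025. Read as a one-sided 97.5% bound, the interval, the alpha, the Farrington-Manning p-value and the 122 all agree at 80% power. This stands as far as it goes: the 97.5% level does not itself conflict with 122. A reader might infer that the interval and the p-value will contradict each other, but that follows only if the interval is two-sided, and the article does not say so. The 40% and 71% figures carry the same condition.

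It does not remove the mismatch. Objective 1 is called one-sided, while objectives 2 and 3 are not and are worded as equivalence. The first set's threshold and sensing objectives pair equivalence with an explicitly two-sided interval. A reader following the article's own usage could fairly take both margins to be meant, and on that reading 122 falls short for sensing even at 0.025 per side.

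A second reply is that 122 is not the trial's size. This stands too. A reader might infer a trial with 40% to 60% power, but the article enrols 470, and Step 4 shows ample sensing power on either reading unless losses are substantial. The analysis exclusions (out-of-window visits, scans not done to protocol, atrial arrhythmia, dislodgment, unstable thresholds) will remove some patients, but the article does not quantify them.

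A third reply is that preferring non-inferiority chooses the hypothesis for the sponsor. This is fair: the article does not rule out interest in both directions, so the fix leaves the choice open.

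**Conclusion.** The point holds in a limited form. For the second-set sensing objective, the stated 122 per group and its 80% power belong to a one-sided, single-margin Farrington-Manning test at 0.025, not to the equivalence hypothesis as worded. Read as equivalence, 122 gives about 60% power (exact 65%) at 0.025 per side, or about 40% (exact 45%) if the 97.5% interval is two-sided; 80% would need 160 or 190 per group.

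The shortfall does not extend equally to capture. At 122 per group, capture equivalence has about 85% power at 0.025 per side and falls below 80%, to about 71%, only if the interval is two-sided.

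The documents do not support a conclusion that the trial is underpowered. The defect is a power statement attached to the wrong test, with the number of margins and the sidedness left open for primary objectives. The figures assume equal true rates at the article's 93% and 96%; the enrolled-size figures also assume the 60% split and equal losses in the two groups.

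**What to change.** Make the hypothesis, bound and size describe one test, by one of two routes.

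1. **If one margin is intended:** state objectives 2 and 3 as non-inferiority (MRI minus control greater than −10 points) at one-sided alpha 0.025. Judge them on a one-sided 97.5% lower bound obtained by inverting the Farrington-Manning test, so that bound and p-value always agree. Keep 122 per group. The cost is wording only, since this is the calculation already done.
2. **If both margins are intended:** say so and state the alpha per side. Replace 122 with 160 per group (0.025 per side) or 190 per group (0.0125 per side). Restate the power for the evaluable part of the 470, with the assumed attrition and analysis exclusions given. The cost is a recalculation and revised text; enrolment need not change unless expected losses exceed roughly 30% or 17–18% respectively.

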## Study design

This study is a prospective, randomized controlled, unblinded, multi-center investigational trial and is being conducted in approximately 75 centers in the United States (US), Canada, Europe and Middle East. After implantation of the Medtronic EnRhythm MRI SureScan system (Medtronic EnRhythm MRI™ SureScan™ pacemaker and Medtronic CapSureFix MRI™ leads), patients are required to have follow-up visits at 2 months, 2.5 months (between 9–12 weeks post-implant an MRI scan or no-MRI scan is performed, depending on randomization), 3 months (1 week post- MRI/no-MRI) and 4 months post-implant (1 month post-MRI scan/no-MRI). Further follow-up is required at 6 months post-implant and every 6 months thereafter until the study ends. Full interrogation of all device information and impedance, sensing and capture function are measured at implant, every follow-up and immediately before and after MRI in the MRI group and at the same time points in the control group. The system must be implanted for more than 6 weeks to allow the Implantable Pulse Generator (IPG) and leads to develop stable pacing and sensing function in the patient prior to allowing the patient to undergo an MRI scan.

A concurrent control group design was selected because the effect of MRI on capture and sensing measurements is unclear. The observed effect in this study will theoretically result from the sum of the natural variation in capture and sensing parameters common to all patients, added to the effect of the MRI examination. Without a randomized control group, it is impossible to isolate the effect of the MRI from the component common to all patients with an IPG system. The possible difference in the electrical measurements due to the MRI scan is precisely what study investigators wish to understand.

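### Second-set sensing objective: the planned unstratified test is valid, but it does not use pre-scan amplitude as a stratum, although this is measured in both groups and predicts success

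*Protocol article*

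**What the plan says.** In the Protocol article, Objectives of the study, second analysis, Primary Objective 3 compares the proportions of sensing successes in the MRI and control groups, separately for atrium and ventricle. A success is a patient "who experience a sense amplitude decrease less than 50" per cent and "whose sense amplitudes remain above an clinically acceptable minimum (1.5 mV for atrium and 5 mV for the ventricle) at one month" after MRI/no-MRI. The proportions are to be shown equivalent: they "are equivalent (Δ = 10%, p_1 _and p_2 _= 93%) between the two groups". The method is stated outright: "The objective will be analyzed using a two-sample 97.5% confidence interval, with p-values from the Farrington-Manning test for equivalence of proportions". No covariate or stratum is named.

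Under Study design, impedance, sensing and capture are measured "immediately before and after MRI in the MRI group and at the same time points in the control group". The pre-scan amplitude is therefore available in both groups.

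Under Sample size and data use for analysis, the article gives "the largest requirements (62 patients per group for the first set, 122 per group for the second set", then raises the second-set total to 470 for attrition and added regulatory requirements.

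**The concern.** The sensing endpoint combines a relative criterion (the fall from the pre-scan reading) with an absolute one (the floor). Using the reading to compute the relative fall does not remove its influence through the floor. Someone starting just above 1.5 mV or 5 mV can fail after a small random drop, and someone starting well above it almost cannot. Part of the spread in outcomes therefore reflects where patients started, and an unstratified comparison counts that part as noise.

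Precision on this objective matters for two reasons. It is the objective that fixes the stated per-group requirement (see the working). All three primary objectives must also be met, and objectives 2 and 3 each have an atrial and a ventricular part. If those four tests were independent (an assumption), joint power at 122 per group would be 0.802² × 0.924² = 0.55.

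**Working it through.** **Inputs from the article.** Sensing: 93% success in both groups, margin 10 points. Capture: the proportions "are equivalent (Δ = 10%, p_1 _and p_2 _= 96%) between the two groups". Alpha 0.025 and power of at least 80% for the second set.

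**Step 1: reproduce the 122.** Farrington-Manning size per group at 1:1, one-sided:

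n = [z(0.975)·√V0 + z(0.80)·√V1]² / Δ²

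V1 = p1(1−p1) + p2(1−p2). V0 is the same expression at the maximum-likelihood proportions restricted to a difference of −0.10.

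- Sensing: the restricted proportions are 0.8556 and 0.9556, so V0 = 0.1660. V1 = 2 × 0.93 × 0.07 = 0.1302. n = (1.960 × 0.4075 + 0.842 × 0.3608)² / 0.01 = 121.5, so 122. Power at 122 is 80.2%.
- Capture: the restricted proportions are 0.8772 and 0.9772, so V0 = 0.1301. V1 = 2 × 0.96 × 0.04 = 0.0768. n = 88.4, so 89. Power at 122 is 92.4%.

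The stated figure is reproduced exactly, and it is the sensing requirement.

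**Step 2: gain from stratifying sensing, at 122 per group.** The article gives neither the spread of amplitudes nor the pre/post correlation, so these are assumed: log-normal amplitudes, log-SD about 0.4-0.5, and success calibrated to 93%. The strata are three pre-scan bands: below the floor, 1 to 1.5 times the floor, and above that. Mantel-Haenszel weights are used. The simulation gives:

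| Assumed pre/post correlation | Fall in variance of the estimated difference |
|---|---|
| 0.6 | about 0-4% |
| 0.7 | 5-16% |
| 0.8 | 19-29% |
| 0.9 | 41-45% |

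Simulated power goes from about 82% (crude) to 82-93% and was not lower in any scenario. Error at the margin was about 1.5-2.6% against the nominal 2.5%.

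In interval terms, the crude 95% half-width is 1.96 × √(0.1302/122) = 6.4 points. Multiplying by the square root of the remaining variance gives:
- 5.4-5.8 points at correlation 0.8 (√0.71 to √0.81);
- 4.7-4.9 points at correlation 0.9 (√0.55 to √0.59).

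The gain shrinks if patients already below the floor are removed. The pre-scan value then explains only 3-16% of outcome variance. The exclusions listed in the article do not remove these patients.

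**Step 3: position at 470 patients.** The Randomization section expects more than 60% of patients at 1:1 and the rest at 2:1. Taking 60% and 40% as the assumption, the MRI share is 0.6 × 0.5 + 0.4 × 0.667 = 0.567, or about 266 against 204. Crude sensing power by the same method:

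| Share of patients not evaluable | Power |
|---|---|
| 0% | 98.3% |
| 20% | 95.3% |
| 30% | 92.4% |
| 40% | 87.9% |
| 48% | about 83% |

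The 122-per-group setting of Step 2 therefore corresponds to losing nearly half of the enrolled patients.

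**Step 4: does the argument carry over to capture?** Capture success is to "experience an acceptable threshold increase less or equal to 0.5 V": a change with no absolute limit, so the floor mechanism is absent. If the pre-scan value and the change correlate at 0, −0.3 or −0.5, the share of variance explained is 0, 2 or 7%. At 122 per group about 122 × 0.04 = 5 failures per group are expected, fewer than 2 per tertile.

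**The case against.** The strongest case against is that nothing here is wrong. Randomisation makes the crude difference unbiased, and its interval already allows for chance imbalance in pre-scan amplitude. Crude simulated error was 2.1-2.9%, close to nominal. The crude test also matches the sample-size calculation and the margin on the marginal difference. With so few failures, adjustment is not free of risk either: an influence-function estimator tried on the same problem gave 3.2-4.5% error at the margin. Supportive stratified analyses may also sit in the full investigational plan, which is not shown.

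Most of this stands, and it limits the point to efficiency. It does not remove the point. The article names the primary test for a pass/fail objective, and the stratified score test did not share the error inflation.

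A reader might infer more than the document supports:

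- **That the pre-scan reading is ignored.** It enters the definitions of both the capture and the sensing endpoints. It is unused only as a stratum.
- **That it largely decides who succeeds.** The article gives no distribution or correlation to show this. About half of the outcome variance is explained only at a correlation near 0.9.
- **That capture has the same weakness or drives the sample size.** Capture has no floor and needs 89 per group.
- **That the trial could be smaller.** The 470 includes allowance for attrition and regulatory requirements.

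**Conclusion.** The point holds for second-set objective 3 (sensing) only, as a low-cost gain in precision and not as the correction of an error. The planned test is valid. The floor makes pre-scan amplitude prognostic, and the reading is available in both groups. How much stratifying would gain cannot be settled from the article: it ranges from almost nothing at a pre/post correlation of 0.6 to a variance reduction of about 45% at 0.9, under log-normal amplitudes and 93% success. With 470 patients and losses up to about a quarter, crude power is already about 94-98%. The practical value is a tighter interval and some protection if the exclusions listed under Sample size and data use for analysis (visits out of window, off-protocol scans, atrial arrhythmia, lead dislodgment, unstable thresholds) remove many patients.

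**What to change.** For second-set objective 3, pre-specify before the data are seen a stratified Farrington-Manning (Miettinen-Nurminen) risk difference and interval with Mantel-Haenszel weights. Stratify by the pre-scan amplitude of the chamber tested, for example below the floor, 1 to 1.5 times the floor, and above. Keep the 10-point margin and the alpha, and report the crude result beside it. State which of the two decides the objective. Leave the capture analysis unchanged.

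The cost is a paragraph of analysis-plan wording and a few lines of code, with no new data and no more patients. The downside is slightly more analysis work and a mildly conservative test if the pre/post correlation is high.
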